# Effects of propranolol on fear of dental extraction: study protocol for a randomized controlled trial

**DOI:** 10.1186/s13063-015-1065-7

**Published:** 2015-11-25

**Keywords:** Dental anxiety, Dental extraction, Tooth extraction, Third molar, Propranolol, Randomized controlled trial

## Abstract

**Background:**

Undergoing an extraction has been shown to pose a significantly increased risk for the development of chronic apprehension for dental surgical procedures, disproportionate forms of dental anxiety (that is, dental phobia), and symptoms of post-traumatic stress. Evidence suggests that intrusive emotional memories of these events both induce and maintain these forms of anxiety. Addressing these problems effectively requires an intervention that durably reduces both the intrusiveness of key fear-related memories and state anxiety during surgery. Moreover, evidence suggests that propranolol is capable of inhibiting “memory reconsolidation” (that is, it blocks the process of storing a recently retrieved fear memory). Hence, the purpose of this trial is to determine the anxiolytic and fear memory reconsolidation inhibiting effects of the ß-adrenoreceptor antagonist propranolol on patients with high levels of fear in anticipation of a dental extraction.

**Methods/Design:**

This trial is designed as a multicenter, randomized, placebo-controlled, two-group, parallel, double-blind trial of 34 participants. Consecutive patients who have been referred by their dentist to the departments of oral and maxillofacial surgery of a University hospital or a secondary referral hospital in the Netherlands for at least two tooth and/or molar removals and with self-reported high to extreme fear in anticipation of a dental extraction will be recruited. The intervention is the administration of two 40 mg propranolol capsules 1 hour prior to a dental extraction, followed by one 40 mg capsule directly postoperatively. Placebo capsules will be used as a comparator. The primary outcome will be dental trait anxiety score reduction from baseline to 4-weeks follow-up. The secondary outcomes will be self-reported anxiety during surgery, physiological parameters (heart rate and blood pressure) during recall of the crucial fear-related memory, self-reported vividness, and emotional charge of the crucial fear-related memory.

**Discussion:**

This randomized trial is the first to test the efficacy of 120 mg of perioperative propranolol versus placebo in reducing short-term (“state”) anxiety during dental extraction, fear memory reconsolidation, and lasting dental (“trait”) anxiety in a clinical population. If the results show a reduction in anxiety, this would offer support for routinely prescribing propranolol in patients who are fearful of undergoing dental extractions.

**Trial registration:**

ClinicalTrials.gov identifier: NCT02268357, registered on 7 October 2014. The Netherlands National Trial Register identifier: NTR5364, registered on 16 August 2015.

## Background

### Epidemiology and current management of fear for dental extractions

Tooth or molar removals are among the most strongly feared procedures in Dentistry and Oral and Maxillofacial Surgery [1, 2]. In the United States, approximately 55 million extractions and surgical removals are carried out each year [3]. In the majority of cases, having a tooth removed causes immediate but generally transitory emotional distress [4–7]. This type of transitory (“state”) anxiety not only produces discomfort but can also induce patient behavior that impedes surgery, thereby increasing operative time and complicating postoperative recovery [8, 9]. Hence, to be capable of effectively performing dental treatment, Oral and Maxillofacial surgeons and specialized dental fear clinics commonly employ oral and intravenous sedatives such as benzodiazepines and nitrous oxide. However, the application of conscious sedation requires thorough training, and sedation-related incidents are common [10]. A publication by the National Health Service of the United Kingdom showed that, in the period between 2004 to 2008, 1,529 incidents were reported regarding conscious sedation with midazolam; in three cases, the patient died [10]. Further disadvantages of these agents include reduced cognitive and motor function, and anterograde amnesia, which may interfere with long-term anxiety reduction [11, 12]. Moreover, to date, only limited evidence exists for the effectiveness of these agents at reducing dental anxiety [13]. Because anxiety treatment failure rates of 88 to 91 % for intravenous sedation and 61-70 % for nitrous oxide have been found at 1-year follow-up after treatment [14], new safe, easily applied and cost-effective interventions for use within the dental and oral surgical setting are warranted.

### Role of traumatic dental experiences in the etiology and maintenance of dental anxiety

Having undergone an extraction had been found to pose an increased risk for developing persistent anxiety [6, 7, 15]. A small portion of approximately 4 to 8 % of patients suffer from elevated dental trait anxiety or even post-traumatic stress disorder (PTSD) symptoms 1 month after surgical removal of their wisdom teeth [6, 7]. This suggests that the psychological impact of a dental extraction may not be limited to temporary distress but also that a dental extraction is a potential psychologically traumatic experience to at least some patients.

A wide array of studies have shown that dental fear and anxiety are deeply rooted in the experience of previous negative dental or other types of distressing and traumatic life events, for example, [15–18]. A recent case-control study (total n = 153) among dental phobic individuals, subthreshold dental phobics and normal controls, showed that apprehension of dental treatment is strongly associated with the presence of memories of earlier distressing events [19]. For example, 97 % of subthreshold (non)phobic individuals have reported a memory of an aversive event, predominantly in the dental setting, that initiated or exacerbated their dental anxiety; this was significantly higher than the proportion of normal controls reporting such a memory [19]. Emotional disturbance, vividness and sense of reliving of these memories were significantly higher in the subthreshold phobic group and dental phobic group than in the normal controls [19]. Notably, normal controls reported lower levels of intrusiveness and avoidance scores (features typically seen in individuals suffering from PTSD) than both phobic and subthreshold phobic groups (all p values < 0.001). This suggests that the memories of the previous distressing dental events that initiated the dental fear play an important role in the maintenance of the individual’s current anxiety and fear response [19]. This is of importance, as research has indicated that dental anxiety is likely to lead to avoidance of dental care with subsequent adverse effects on oral health status and quality of life [20].

### Rationale for testing the effects of perioperative propranolol on dental anxiety

Treating apprehension or fear of dental treatment effectively requires an intervention that reduces the (1) state anxiety during the surgery, (2) the emotional charge of key fear-related memories, and (3) patients’ level of dental trait anxiety. There are indications that the ß-blocker propranolol is capable of bringing about these anxiolytic effects.

Propranolol, a ß_1,2_-adrenoreceptor antagonist, competes at the receptor level with catecholamines, thereby blocking their orthosympathetic effects [21]. Clinically, propranolol is used widely to target peripheral sites of the noradrenergic system to treat hypertension [22], coronary artery disease [23] and tachyarrhythmias [24]. In addition, propranolol can be deployed to block ß-adrenoreceptors in the central nervous system, as the lipophilic compound readily enters the blood-brain-barrier.

Several trials studying off-label use of propranolol have been conducted, such as its application in the treatment of high levels of trait anxiety [25–27], substance disorder and withdrawal symptoms [28], schizophrenia [29], autism [30], and aggression [31]. In addition, propranolol has been shown to mitigate milder distressing states such as exam nerves [32–34], stage fright [35], performance anxiety among musicians [36] and surgeons [37], and fear of undergoing surgery [38–40]. Evidence suggests that propranolol positively influences dental state anxiety and reduces the storage of fear memories.

### Evidence for effects of propranolol on dental state anxiety

Currently one randomized, controlled clinical trial (RCT) evaluating the state anxiolytic effects of propranolol in dental phobia has been published. It showed that, as compared to placebo, 80 to 120 mg of oral propranolol significantly diminished self-reported state anxiety during injection of local dental anesthesia (self-reported anxiety about the injection: 5.5 (2.75) versus 7.45 (2.0), p = .033, one-tailed) [41]. A limitation to this study is that follow-up data were lacking. This means that to date, the long-term effects of propranolol on dental trait anxiety are unknown.

### Evidence for effects of propranolol on fear memory storage

Because traumatic memories seem to play a key role in the maintenance and severity of dental trait anxiety [19], propranolol has potential for the treatment of this condition. Preclinical studies have shown that propranolol has the capacity to selectively block the protein synthesis required for the storage of aversive (emotional) memory while sparing declarative memory (factual memory) [42–50]. A recent meta-analysis of eight experiments with healthy human volunteers (total n = 308) supports this line of reasoning, as it showed that, compared to placebo, propranolol administered before memory reactivation reduces the expression of cue-elicited fear responses [51]. To date however, there is only one clinical trial supporting the effects of propranolol on the reconsolidation of traumatic memories. In this study, with chronic PTSD patients (n = 19), it was found that 40 mg of short-acting oral propranolol given prior to imaginary exposure to the disturbing memory of the event, followed by 60 mg of long-acting oral propranolol, significantly reduced physiologic responding to the memory one week later [52]. Although preclinical evidence is promising, clinical evidence is scarce. Therefore, the reconsolidation blocking capacities of propranolol need further research attention.

### Primary aim

The primary aim of this study is to determine whether administration of the active substance (two 40 mg propranolol capsules 1 hour prior to dental extraction, followed by one 40 mg capsule immediately postoperatively) results in a significantly greater reduction of dental trait anxiety in patients with self-reported high to extreme fear in anticipation of dental extraction, compared to the effects of the placebo comparator, from baseline to 4-week follow-up appointment.

### Secondary aims

The secondary aims are to determine whether the use of propranolol in patients with high self-reported levels of fear in anticipation of tooth or molar removal results in the following:a significantly greater reduction of self-reported intraoperative (state) anxiety, compared to the placebo comparator, from baseline to the 4-week follow-up appointment;a significantly greater decrease of physiological responding during recall of the crucial fear-related memory, compared to the placebo comparator, from baseline to the 4-week follow-up appointment;a significantly greater decrease in specific phobia diagnoses, compared to the placebo comparator, from baseline to the 4-week follow-up appointment;a significantly greater reduction of self-reported vividness and emotional charge of the crucial fear-related memory scores, compared to the placebo comparator, from the baseline to the 4-week follow-up appointment.

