#### First dental extraction procedure

One hour and 15 minutes before the surgery, participants will be approached by the investigator. They will then receive the first two capsules of study medication. The intervention group will receive 80 mg of oral propranolol (2 capsules) 1 hour and 15 minutes prior to treatment, and 40 mg of oral propranolol (1 capsule) directly after treatment. The control group will receive oral placebo capsules in the same order. The following hour is reserved to allow time for achieving an optimal plasma concentration of propranolol.

In the period between ingestion of the study medication and the surgery, a 30-minute screening by an investigator will take place (see paragraph: “Study outcome measures”). All outcomes will be registered on a case report form (CRF). After the interview, the patients will be guided back to the waiting room by the investigator. Next, they will be invited into the operating room by their surgeon. The surgeon will be either a senior staff member or a resident in Oral and Maxillofacial Surgery. During this first procedure, a prilocaine 3 % with felypressin (1:850,000) solution will be administered as local intraoral anesthetic to prevent a possible unwanted α-pressor reaction; a rare and potentially harmful pharmacological interaction of ß-adrenoreceptor antagonists with adrenaline that may result from the intravascular injection of the local anesthetic, causing bradycardia and hypertension.

In case of patients with a high level of fear of dental extractions, the surgeon will be notified that the patient has a “high or extreme” fear of dental extractions (the level of fear is not specified further) and is instructed to treat the patients accordingly.

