#### Second dental extraction procedure

At the 1-month follow-up, a second dental extraction at the hospital will be performed, this time without the study medication. Administration of all questionnaires before and after the procedure will be repeated, but this time, no full-intrusions interview will be conducted. During the second procedure, a regularly used local anesthetic solution of articaine 4 % with adrenaline (1:200,000) will be administered. At completion, the surgeon will fill out another CRF, and the participant will be asked to keep another “intrusions diary”.

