### Study outcome measures

Dependent variables were derived from the questionnaires listed below (see Tables 1 and 2).

**Table 1 Tab1:** Primary and secondary study outcome measures

		Measures			
		Primary outcome	Secondary outcomes		
		Trait anxiety (S-DAI)	State anxiety (VAS score)	Vividness/emotional charge (M1) propensity (VAS scores)	Physiological response (HR/BP)
Screening (t = 0)	Screening interview				
Intervention (t = 1)	Preoperative interview	X		X	X
	Postoperative interview		X		
Follow-up (t = 2)	Preoperative interview	X		X	X
	Postoperative interview		X		

*Note:*
*BP* blood pressure, *HR* heart rate, *M1* crucial fear-related memory, *S-DAI* Short version of the Dental Anxiety Inventory, *VAS* visual analog scale

**Table 2 Tab2:** Tertiary outcome measures

		Measures							
		Operative variables/qualitative aspect of the surgical experience (VASs)	Test of blind	IES	FCDS	Qualitative aspect of memory M2 (VASs)	Qualitative aspect of memory M1 (VASs)	Intrusions diary	Specific phobia diagnosis
Screening (t = 0)	Screening interview				X				X
Intervention (t = 1)	Preoperative interview			X			X		
	Postoperative interview	X	X			X		X	
Follow-up (t = 2)	Preoperative interview			X	X	X	X		X
	Postoperative interview	X						X	

*Notes:*
*FCDS* fear of stimuli compromising the dental setting, *IES* Impact of Event Scale - Revised, *M1* crucial fear-related memory, *M2* memory of recent dental extraction procedure, *VAS* visual analog scale

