#### Secondary outcome measures

The self-reported state anxiety during dental treatment from baseline to 1-month follow-up will be indexed using a visual analog scale (Table 1). Patients are asked to rate the question “How much anxiety did you experience during the last treatment” using a standardized continuous self-report VAS ranging from “no anxiety at all” 0 to “extreme anxiety” 100.

Change from baseline to 1-month follow-up in self-reported vividness and emotional charge of the crucial fear-related memory will be measured using visual analog scales that assess key characteristics of the traumatic memory that initiated or exacerbated the dental anxiety (M1) (Table 1). Patients will be asked to rate the questions “how vivid or detailed is the memory, if you bring up the memory now” and “how much emotion does the memory evoke, if you bring up the memory now” using a continuous self-report VAS ranging from “no (anxiety/emotion) at all” (0) to “extremely much (anxiety/emotion)” (100).

Change from baseline to 1-month follow-up in physiological parameters during recall of the crucial fear-related memory (M1), will be assessed by bringing up the memory (M1) while the psychophysiological response (heart frequency per minute and blood pressure in mm Hg) will be indexed using an upper arm blood pressure measuring device (CE: 0297) (Table 1).

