### Statistical analysis plan

The distributions of demographic variables and quantitative data will be displayed in tables. Associations between categorical variables will be analyzed using the Chi^2^-test. Differences between the propranolol and placebo condition on continuous variables will be analyzed using the independent-samples t-test. Two-way (condition by time) repeated measures ANOVA will be used to compare the propranolol and placebo condition on the dental anxiety reduction between the first and second extraction, possibly with the baseline score as a covariate (if differences exist at baseline). The alpha is set at a significance level of 5 %.

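### State anxiety is defined as a reduction from baseline, but its first rating is made on study drug, so the change subtracts the acute effect and misleads unless the drug-free effect is larger

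*Protocol article*

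**What the plan says.** The protocol article defines this outcome as a change in two places. Under Secondary aims it is "a significantly greater reduction of self-reported intraoperative (state) anxiety, compared to the placebo comparator, from baseline to the 4-week follow-up appointment". Under Secondary outcome measures: "The self-reported state anxiety during dental treatment from baseline to 1-month follow-up will be indexed using a visual analog scale". The item itself reads "How much anxiety did you experience during the last treatment", scored 0 to 100.

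Table 1 (Study outcome measures) marks the state-anxiety VAS at two points only: the postoperative interview at the intervention visit (t = 1) and the postoperative interview at follow-up (t = 2). It has no mark at screening or at either preoperative interview.

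On exposure, First dental extraction procedure says: "The intervention group will receive 80 mg of oral propranolol (2 capsules) 1 hour and 15 minutes prior to treatment". The Active substance section gives the purpose of that preoperative dose as lowering perioperative state anxiety. At follow-up, "a second dental extraction at the hospital will be performed, this time without the study medication".

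The Statistical analysis plan section uses a condition-by-time repeated measures ANOVA to "compare the propranolol and placebo condition on the dental anxiety reduction between the first and second extraction", and allows the baseline score as a covariate if the arms differ at baseline. It also lists an independent-samples t-test for continuous variables, without naming outcomes or time points.

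**The concern.** A reduction from baseline measures a treatment effect only if the baseline precedes treatment. Here the first rating is the result of treatment: it describes the surgery that the preoperative dose was meant to make less frightening. Subtracting the second rating from it removes the acute drug effect from the answer.

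The article's Discussion abstract and its rationale section both present lower anxiety during surgery as one of the effects under test, and this VAS is the patient-reported measure of it. Under the stated contrast, a drug that calms patients during the first extraction and then wears off would appear worse than placebo. The article links a reduction in anxiety to routine prescribing, so a wrong sign on this outcome could mislead. Replacing the contrast after a reversed result has been seen would look post hoc.

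**Working it through.** **1. The plan's own figure.** The only sample size stated is for the primary outcome (S-DAI), tested as a condition-by-time interaction. Inputs from Sample size calculation: f = 0.25, correlation 0.50, two measurements, two arms, alpha 0.05, power 0.80. With λ = f² × N × m / (1 − ρ) = 0.0625 × 34 × 2 / 0.50 = 8.5 on 1 and 32 degrees of freedom, power is 0.807. N = 32 gives 0.781. The stated total of 34 reproduces. No power is stated for state anxiety.

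**2. What the change contrast estimates.** Let placebo patients average μ at the first extraction and μ − h at the second. Let propranolol lower the first rating by D and the second by rD.

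- Placebo reduction: μ − (μ − h) = h.
- Propranolol reduction: (μ − D) − (μ − h − rD) = h − D + rD.
- Difference, propranolol minus placebo: (r − 1) × D.

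This is negative for r < 1, zero at r = 1 and positive only for r > 1. The sign needs no numerical assumption about D or the scale.

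**3. Illustrative size.** The cited dental trial (Evidence for effects of propranolol on dental state anxiety) gives 5.5 (2.75) versus 7.45 (2.0), so D = 7.45 − 5.5 = 1.95. Reading the brackets as SDs, pooled SD = √((2.75² + 2.0²)/2) = 2.40 and D/SD = 0.81. Assumptions: 17 per arm (34 at 1:1), two-sided 0.05, and the S-DAI correlation of 0.50 borrowed for the VAS, so SD of change = 2.40 × √(2 × 0.50) = 2.40. Noncentral t on change scores:

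| r (share persisting) | Difference in reduction | P(significant, favours propranolol) | P(significant, favours placebo) |
|---|---|---|---|
| 0 | −1.95 | < 0.001 | 0.63 |
| 0.5 | −0.98 | 0.001 | 0.21 |
| 1 | 0 | 0.025 | 0.025 |
| 1.5 | +0.98 | 0.21 | 0.001 |

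At r = 0, the chance of a significant result for placebo is 0.49 if the correlation is 0.3 and 0.84 if it is 0.7.

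**4. The direct comparison.** Comparing arms on the first-extraction VAS, with D = 1.95, SD 2.40 and 17 per arm, gives power 0.63 (normal approximation 0.66). The chance of a significant result in the wrong direction is below 0.001.

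**5. The covariate rule, if applied here.** An arm difference in the first VAS may be the drug effect itself, so a working drug tends to trigger the rule. With equal SDs the regression slope equals ρ, and the adjusted contrast becomes rD − ρD = (r − ρ) × D. At ρ = 0.50 and r = 0 that is −0.5 × 1.95 = −0.98; at r = 0.5 it is zero. Adjustment moves the point at which the sign changes, but the result is still neither the acute effect D nor the carry-over effect rD.

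**The case against.** **The drug might work better later.** The trial proposes two mechanisms, acute anxiolysis and blocked reconsolidation, and the postoperative capsule is aimed at the second. If the drug-free effect exceeded the acute effect, the unadjusted contrast would have the intended sign. This stands: a reader might infer that any working drug must give a null or reversed result, and the documents do not exclude r > 1. Power would still be low, at 0.21 for r = 1.5.

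**The ANOVA may be meant for the S-DAI only.** The Statistical analysis plan section speaks of dental anxiety without naming state anxiety, and the sample size section uses similar terms for the S-DAI. It also lists a t-test that could be applied to the first-extraction VAS, and the abstract describes the outcome simply as anxiety during surgery. A reader might infer that the ANOVA and covariate rule are assigned to state anxiety; the text does not say so. But nothing assigns the t-test to this aim either, and the aim and the outcome definition both still state a change from baseline. That conflicts with Table 1 whichever test is used, so it is not a detail left to an analysis plan.

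**The size is illustrative.** This also stands. The cited figures concern anxiety about the injection, and no scale is given. Multiplying by ten to reach a 0–100 VAS would turn 1.95 into 19.5 points, but that rests on an assumed scale and on zero persistence. It should not be read as an expected bias.

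**Conclusion.** The point holds with its condition attached. The state-anxiety baseline is an on-treatment rating, so the change stated in the aim cannot isolate the acute effect. Without covariate adjustment it shows no difference when the effect fully persists (r = 1) and favours placebo when the effect fades (r < 1). This follows from Table 1, the item wording and the dosing schedule alone. The probabilities rest further on the cited trial's figures, on brackets read as SDs and on a correlation the article does not give for this outcome.

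This is a should-fix. It concerns one secondary outcome, both ratings are already collected, and the S-DAI analysis and N = 34 are unaffected.

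**What to change.** - In Secondary aims and Secondary outcome measures, redefine the outcome as the between-arm comparison of the VAS at the first extraction (acute effect, on drug). Test the between-arm comparison at the second extraction separately (carry-over effect, off drug).
- Remove the from-baseline wording for this outcome. Keep the first-to-second change as descriptive at most.
- In the Statistical analysis plan section, state that the condition-by-time ANOVA and the baseline-covariate rule do not apply to state anxiety, and name the test that does.
- Adjust for the baseline S-DAI only if it is confirmed to be completed before the capsules are taken. First preoperative assessment describes questionnaires in connection with arrival before ingestion, First dental extraction procedure places an outcome screening between ingestion and surgery, and Table 1 says only that the interview is preoperative. These passages must be reconciled. Otherwise compare the arms unadjusted.

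The cost is wording and analysis only, with no new data, visits or patients. It should be settled before unblinding.
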